### Randomization and blinding procedures

Following the initial assessment, eligible volunteers will be randomly assigned to two experimental groups if they meet the inclusion criteria by the secretariat of the Pulmonology Department of the GCHAA. The randomization will be carried out using sealed envelopes. Individuals will have their allocation concealed through the use of sealed envelopes that are sequentially numbered and opaque.
^
36
^ The envelopes will be opened only by the primary researcher, who is responsible for the research project and coordination of the study. The pulmonologist who will perform lung function testing on all participants (well-maintained and regularly calibrated equipment), diagnose asthma and perform the measure of chest expansion, the radiologist who will perform the ultrasonography (US), and the two separate physical therapists, who will implement the DMRT and BRE will be unaware of the group allocation.

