### Initial assessments

A pulmonologist of GOHK with years of experience diagnosing and treating asthma patients will examine the chest expansion, the pulmonary function, and diagnosis of asthma. The radiologist will perform the US assessment, and the secretariat of the GOHK will administer the questionnaires in a random order and collect all data.

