**Interventions**

The pulmonologist and the main researcher of the protocol will organize two online sessions with all the participants after the randomization. In one session, participants will be informed by the pulmonologist about (a) general asthma information, (b) asthma triggers, (c) recognition of asthma symptoms, (d) medication and proper use of asthma medications (inhaler techniques), (e) smoking, and (f) asthma control (symptom control/future risk domains/long-term goals).
^
38
^ As for the last domain (asthma control), information will be provided regarding, (i) the dynamic changes of asthma, (ii) the recognition of these changes based on PEF values and symptoms, (iii) the importance of early detection of clinical signs of worsening and the immediate initiation of appropriate medication.

At the second online session the participants will be informed by the main researcher about (a) the breathing pattern, (b) the pathological pattern of breathing that is developing both in stable phase and in paroxysm,
^
39
^ (c) the role of physiotherapy and specifically about the BRE in PR, (d) the formation of a trusting relationship between a person living with asthma and a medical professional (e) the importance of self-efficacy in asthma self-management
^
40
^
^–^
^
43
^ and (f) the self-efficacy enhancement process.

Following the two online sessions, there will be a discussion between patients and health professionals (pulmonologist - main researcher) lasting approximately one hour, during which patients can share their objectives, values, apprehensions, support and commendations. The structure of the online session will be determined by a) the long-term objectives for asthma management
^
5
^ and b) the health belief model.
^
44
^
^,^
^
45
^ Regarding the treatment sessions, every participant will receive twelve sessions twice weekly for six weeks, lasting one hour per session. Individual sessions will be provided in patients’ homes under the same conditions (
*e.g.*, day, time of day, temperature, therapeutic bed, and patient’s position).

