Physiotherapy intervention will be provided by two physical therapists, trained by the professor of chest physiotherapy and the professor of manual therapy respectively, at the Physiotherapy Department, UNIWA. Any departure from the administration of treatment sessions (such as missing more than one appointment) or any exacerbation of symptoms will lead to exclusion. Brief descriptions of the interventions planned for each group are provided below.

Intervention Group: This group will receive MDRT plus BRE. MDRT is intended to stretch and mobilize the diaphragmatic muscle fibers indirectly. MDRT will be applied as described by Rocha and his colleagues.
^
18
^

MDRT: Participants will be instructed to lie in a supine position with relaxed limbs. The therapist will be positioned at the patient’s head. Manual contact will be made using the hypothenar region and the last three fingers bilaterally, placed under the seventh to tenth rib costal cartilages. The therapist’s forearms will align towards the patient’s shoulders. During inhalation, the therapist will apply gentle pulling and lateral elevation of the ribs in the inspiratory phase at the points of contact. As the participant exhales, the therapist’s touch will deepen towards the inner costal margin while maintaining resistance. This connection will further deepen within the costal margin in subsequent respiratory cycles. Regarding respiratory volumes, patients will be instructed to breathe progressively deeper from set to set, aiming for maximal diaphragmatic excursion and stretch. It is essential to ensure that the therapist’s grip on the lower thoracic aperture is maintained throughout. The entire process will consist of two sets of 10 repetitions, separated by a 1-minute interval lasting 10 minutes.
^
46
^

BRE: BRE will be conducted for 30 minutes. The primary objective of these exercises is to mitigate hyperventilation, hypocapnia, and dysfunctional breathing—common symptoms in individuals with asthma.
^
47
^ The initial step involves identifying and inhibiting an abnormal upper thoracic respiratory pattern and re-education of diaphragmatic and slow nasal breathing. Additionally, brief respiratory pauses will be introduced after each exhalation.
^
48

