	**Practice diaphragmatic and nose breathing retraining**	- Half-lying supine position - Pillows behind the head & knees - one relaxed hand over the stomach and the other on the upper chest and clavicle	- *“Close your mouth and try to breathe easily, slowly and softly through your nose”* - *“Be careful not to inhale with “big” breaths, try during inhalation to raise only the stomach”* - *“Exhalation is passive through the nose and lets your stomach fall gently”*		1S x 5BC	
	**Slow breathing and controlled breath holding after exhalation**	- Half-lying supine position - Pillows behind head and knees - One relaxed hand over stomach and the other on upper chest and clavicle	- *“Close your mouth and try to breathe easily, slowly and softly through your nose”* - *“Relax your shoulder & chest”* - *“Try to slow down your breaths”* - *“Sometimes it helps to count in your mind while you are breathing, e.g. breathe in for a slow count of 2 and breathe out for a slow count of 3until feel empty your stomach”* - *“Keep empty your stomach for 3-5 seconds”*		1S x 10BC	
	**New breathing pattern in everyday life activities and various positions**	- Supine - Semi-sitting - Sitting	- *“Try to breathe in and out slowly and through the nose, even in the most challenging conditions”* - *“You will be able to recognize faulty breathing patterns, and you will be able to correct them”* - *“Try to use a calendar or a mobile phone reminder to implement a diaphragmatic slow nose breathing pattern and breathing exercises”*		3S x 5BC	
	**Breathing control in speech**	- Supine - Semi-sitting - Sitting	- *“You must budget airflow to control the number of words you say per breath and the tone and loudness of particular words in a sentence”* - *“Apply a slow, through the nose, diaphragmatic breathing pattern at speech (max 4-6 words spoken during slow exhalation, with breathing pauses, and slow inhalations)”* - *“Breathe out so that your lungs feel empty, and, before inhaling again”* - *“At yawning and at sighing close your mouth”* - *“Poor voice quality (hoarseness, roughness, or a strained/strident voice) results from inadequate or badly controlled airflow. Speech prosody: rhythm and intonation”*		3S x 5BC	

Control Group: This group will receive only BRE, as mentioned in the intervention group.

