^ By placing the tape measure at the level of the axilla (about the level of the sternal angle of Louis), the level of the xiphoid process, or between the xiphoid process and the umbilicus, the therapist identifies the upper, middle, and lower chest wall expansion, respectively. The therapist should repeat the measurement at least three times for each level for higher fidelity.
^
51
^ A tape measure (in centimeters) will assess the variance between values recorded during deep inhalation and exhalation, with greater values signifying improved results.
^
51
^ Norms have been developed according to age and sex.
^
60
^

**
*Secondary outcome measures*
**

**Nijmegen Questionnaire (NQ):** The Nijmegen Questionnaire is a reliable and valid tool for assessing dysfunctional breathing
^
62
^ in clinical practice and research. It is designed to identify the Hyperventilation Syndrome (HS). A score greater than 23 indicates the presence of HS in the general population. The NQ has shown 91% sensitivity and 95% specificity.
^
61
^
^,^
^
62
^ In previous research, NQ scores of 20, 22 and 23 have been used as cut-off scores to detect HS in subjects with and without asthma.
^
63
^
^–^
^
65
^ The NQ questionnaire has been validated in Greek adults with asthma, providing evidence of validity and reliability of measurements with a cut-off score of >17.
^
66
^

**Asthma control test (ACT):** The ACT questionnaire is a valid and reliable clinical and research tool.
^
67
^ Its quick completion time is one of its key features. It has five items, all about the most recent four weeks.
^
68
^
^,^
^
69
^ The ACT evaluates the frequency of wheezing and other general asthma symptoms and the need for emergency control self-assessment. The score ranges from 5 (poor control of asthma) to 25 (good control of asthma). An ACT score >19 indicates controlled asthma. The ACT has been validated in the Greek population with asthma and has shown high indices of internal consistency (0.72) and test–retest reliability (IR = 0.85).
^
59
^

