**Data collection methods**

Data regarding the outcomes pre and post-intervention will be meticulously collected from the main researcher. The collected information will undergo a thorough examination to analyze the outcomes. Throughout the study, the professor of chest physiotherapy (supervisor) will closely oversee the main researcher administering the study’s data. To ensure the patient adheres to the study, timely messages will be sent to their mobile phones, providing information and reminders regarding upcoming sessions. A 10% drop-out rate has been considered in the sample size calculation, thus minimizing potential interference with the study results.

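### The protocol claims masking for a therapist who cannot be masked, and does not show that the self-reported outcomes are collected by people unaware of allocation

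*Protocol article*

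**What the plan says.** All references are to the protocol article.

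- **Who is said to be masked.** Randomization and blinding procedures lists the pulmonologist (lung function and chest expansion) and the radiologist (ultrasound), and adds that "the two separate physical therapists, who will implement the DMRT and BRE will be unaware of the group allocation". The primary researcher, the secretariat and the participants are not on that list.
- **What each arm receives.** Interventions says of the experimental arm: "This group will receive MDRT plus BRE". Of the control arm it says: "This group will receive only BRE, as mentioned in the intervention group". No sham manual contact is described.
- **Who handles allocation.** Randomization and blinding procedures has the Pulmonology Department's secretariat assign participants. It also says: "The envelopes will be opened only by the primary researcher".
- **Who handles outcome data.** Data collection methods says: "Data regarding the outcomes pre and post-intervention will be meticulously collected from the main researcher". Initial assessments says that "the secretariat of the GOHK will administer the questionnaires in a random order and collect all data".
- **Who measures chest expansion.** Recruitment procedures, Randomization and blinding procedures and Initial assessments all name the pulmonologist. In the chest wall expansion paragraph of Outcome measures, "the therapist identifies the upper, middle, and lower chest wall expansion, respectively".
- **How the design is presented.** The Discussion counts allocation concealment and masking of the examiners among the features that make the findings reliable.

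**The concern.** A masking statement tells readers which outcomes were protected from knowledge of treatment. If it includes someone who must know the arm, it is wrong on its face and casts doubt on the rest of the list.

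The overlap of tasks matters for a different reason. Participants can tell whether they receive a hands-on technique, and the Consent section says they will be given a translated copy of the protocol, so they cannot be presumed masked. Their self-reports are therefore already open to expectation. If the person who administers or receives those reports also knows the arm, a second route for bias is added: prompting, clarifying answers, chasing missing forms or resolving unclear entries differently by arm. That second route can be closed by design. At stake are the credibility of the self-reported secondary outcomes and the accuracy of the strength claimed in the Discussion.

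**Working it through.** The point rests on no figure in the plan, and no arithmetic beyond a count applies. The check is to set the sections side by side.

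1. **Can the MDRT therapist be unaware of allocation?** MDRT is hands-on contact at the lower costal margin, given in the experimental arm only. Whoever applies it knows that participant's arm. Interventions says the two therapists were trained in chest physiotherapy and manual therapy respectively, which suggests that one gives BRE and the other MDRT. On that reading the MDRT therapist treats experimental participants only, and the BRE therapist could in principle stay masked because both arms receive BRE. If instead each therapist gives both treatments, neither can be masked in the experimental arm. Under either arrangement the claim for both therapists fails.

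2. **Does the envelope opener touch outcome data?** The primary researcher alone opens the envelopes and so knows every allocation. Data collection methods names the main researcher for outcome data both before and after treatment. I read the two titles as one role, and the word from in that sentence as by. The following sentences concern examining and administering the data, so collection could mean direct assessment or only collation. The text does not settle which, and no section has this researcher measuring an outcome.

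3. **Does the secretariat touch outcome data after allocation?** It assigns participants, and it is the only party named as administering questionnaires. That sentence stands under Initial assessments, and randomisation is said to follow the initial assessment. Its role at weeks 6 and 12 is therefore an inference from its collecting all data and from no other administrator being named. Its knowledge of the arm is also not established, because only the primary researcher opens the envelopes. I take the two hospital abbreviations used in these sections to mean the same hospital.

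4. **Which outcomes are affected?** Outcome measures lists seven:
   - Ultrasound excursion (primary): radiologist, stated as blinded.
   - Chest expansion (primary): pulmonologist, stated as blinded, apart from the one reference to a therapist.
   - MIP/MEP: no assessor explicitly named, and nothing gives it to someone who knows the allocation.
   - NQ, ACT, SF-12v2 and Borg: self-reported, with no masked collector stated for weeks 6 and 12.

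   The count for which masked collection is not shown because of the named overlaps is 4 of 7, all secondary.

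**The case against.** The strongest reply is that the two people who measure the primary outcomes are stated to be unaware of allocation, so the Discussion's claim about examiners is defensible for those outcomes. The secretariat sentence may describe baseline work only, and the main researcher's collection may be custody of data rather than assessment. All of this stands. It limits the reach of the point to the therapist statement and the self-reported outcomes.

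Four stronger readings are tempting and are not supported:

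- **That every outcome is biased toward MDRT.** The documents establish neither the direction nor the size of any bias, and both primary outcomes have assessors stated as blinded. Any numerical inflation of the false-positive rate would rest on a freely chosen bias.
- **That the pulmonologist is unmasked.** Interventions says the pulmonologist and main researcher "will organize two online sessions with all the participants after the randomization", followed by a discussion of about an hour. The content is the same for all participants. Disclosure of the arm is a risk, as in any trial with unmasked participants, and not a demonstrated failure.
- **That a therapist measures a primary outcome.** The therapist wording in the chest expansion paragraph reads as a general description of the method, and three other sections name the pulmonologist. It is a wording conflict to tidy up.
- **That the secretariat knowingly collects follow-up data by arm.** As set out above, both its follow-up role and its knowledge of the arm are inferred.

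Timing also limits what can be changed. The trial started in January 2023 with completion scheduled for January 2024, the protocol version is dated 29/09/2023, and Protocol amendments says no further modifications could be made. That does not justify leaving an inaccurate masking statement in place.

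**Conclusion.** The statement that both therapists are unaware of allocation is wrong as written. This is certain for whoever delivers MDRT and needs no assumption beyond the described content of the arms. The overlap between opening the envelopes and collecting outcome data is also in the text, on the assumption that the primary and main researcher are the same role; whether it involves contact with participants' responses is unresolved. The secretariat's overlap is an inference.

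The consequence is bounded. Four of seven outcome measures, all secondary and self-reported, are not shown to be collected under masking. Biased collection of these is plausible but not demonstrated, and no size can be attached to it from the documents.

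**What to change.** 1. In Randomization and blinding procedures, state that participants and the MDRT therapist are not masked. Limit the blinding claim there and in the Discussion to the radiologist and the pulmonologist.
2. At weeks 6 and 12, have participants complete NQ, ACT, SF-12v2 and Borg themselves on coded forms that do not pass through the main researcher or any member of the secretariat who knows the allocation. Say in Data collection methods whether the main researcher's role is assessment or collation.
3. Ask participants not to tell the assessors which arm they are in.
4. In the chest wall expansion paragraph, name the pulmonologist, in line with the other three sections.

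The cost is slightly more form handling and a less favourable blinding statement. Items 2 and 3 can apply only to assessments still to come; for those already done, the report should say who collected the questionnaires and whether they knew the arm. Holding the online sessions before envelopes are opened would lessen the chance of disclosure to the pulmonologist, but could apply only to participants not yet randomised, so it is optional.

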### Participants and eligibility

The pulmonologist of the trial will approach all eligible patients for recruitment into the study. They will be assessed through a set of questions to confirm eligibility. All patients will be requested to provide written informed consent (signed by the main researcher, the subject, and two witnesses) to participate in the study, including permission to publish results, with the understanding that they can withdraw at any time.

### Participants’ characteristics

At least 24 adults will be recruited for the study.

Inclusion criteria: aged 18-60 years, diagnosed with stable asthma
^
37
^ and correct use of the inhaler technique.

Exclusion criteria: Participation in other physical therapy methods, the presence of cardiopulmonary conditions, prior cardiothoracic or abdominal surgeries, recent chest wall or abdominal trauma, unstable hemodynamic parameters (systolic arterial pressure >140 mmHg and diastolic >90 mmHg), inability to comprehend verbal instructions required for outcome assessments, pregnancy, neurological ailments, and concurrent involvement in interventional programs.

### Initial assessments

A pulmonologist of GOHK with years of experience diagnosing and treating asthma patients will examine the chest expansion, the pulmonary function, and diagnosis of asthma. The radiologist will perform the US assessment, and the secretariat of the GOHK will administer the questionnaires in a random order and collect all data.

**Interventions**

The pulmonologist and the main researcher of the protocol will organize two online sessions with all the participants after the randomization. In one session, participants will be informed by the pulmonologist about (a) general asthma information, (b) asthma triggers, (c) recognition of asthma symptoms, (d) medication and proper use of asthma medications (inhaler techniques), (e) smoking, and (f) asthma control (symptom control/future risk domains/long-term goals).
^
38
^ As for the last domain (asthma control), information will be provided regarding, (i) the dynamic changes of asthma, (ii) the recognition of these changes based on PEF values and symptoms, (iii) the importance of early detection of clinical signs of worsening and the immediate initiation of appropriate medication.

At the second online session the participants will be informed by the main researcher about (a) the breathing pattern, (b) the pathological pattern of breathing that is developing both in stable phase and in paroxysm,
^
39
^ (c) the role of physiotherapy and specifically about the BRE in PR, (d) the formation of a trusting relationship between a person living with asthma and a medical professional (e) the importance of self-efficacy in asthma self-management
^
40
^
^–^
^
43
^ and (f) the self-efficacy enhancement process.

Following the two online sessions, there will be a discussion between patients and health professionals (pulmonologist - main researcher) lasting approximately one hour, during which patients can share their objectives, values, apprehensions, support and commendations. The structure of the online session will be determined by a) the long-term objectives for asthma management
^
5
^ and b) the health belief model.
^
44
^
^,^
^
45
^ Regarding the treatment sessions, every participant will receive twelve sessions twice weekly for six weeks, lasting one hour per session. Individual sessions will be provided in patients’ homes under the same conditions (
*e.g.*, day, time of day, temperature, therapeutic bed, and patient’s position).

Physiotherapy intervention will be provided by two physical therapists, trained by the professor of chest physiotherapy and the professor of manual therapy respectively, at the Physiotherapy Department, UNIWA. Any departure from the administration of treatment sessions (such as missing more than one appointment) or any exacerbation of symptoms will lead to exclusion. Brief descriptions of the interventions planned for each group are provided below.

Intervention Group: This group will receive MDRT plus BRE. MDRT is intended to stretch and mobilize the diaphragmatic muscle fibers indirectly. MDRT will be applied as described by Rocha and his colleagues.
^
18
^

MDRT: Participants will be instructed to lie in a supine position with relaxed limbs. The therapist will be positioned at the patient’s head. Manual contact will be made using the hypothenar region and the last three fingers bilaterally, placed under the seventh to tenth rib costal cartilages. The therapist’s forearms will align towards the patient’s shoulders. During inhalation, the therapist will apply gentle pulling and lateral elevation of the ribs in the inspiratory phase at the points of contact. As the participant exhales, the therapist’s touch will deepen towards the inner costal margin while maintaining resistance. This connection will further deepen within the costal margin in subsequent respiratory cycles. Regarding respiratory volumes, patients will be instructed to breathe progressively deeper from set to set, aiming for maximal diaphragmatic excursion and stretch. It is essential to ensure that the therapist’s grip on the lower thoracic aperture is maintained throughout. The entire process will consist of two sets of 10 repetitions, separated by a 1-minute interval lasting 10 minutes.
^
46
^

BRE: BRE will be conducted for 30 minutes. The primary objective of these exercises is to mitigate hyperventilation, hypocapnia, and dysfunctional breathing—common symptoms in individuals with asthma.
^
47
^ The initial step involves identifying and inhibiting an abnormal upper thoracic respiratory pattern and re-education of diaphragmatic and slow nasal breathing. Additionally, brief respiratory pauses will be introduced after each exhalation.
^
48
^ Subsequently, BRE aims to integrate the new breathing pattern into daily life. This stage focuses on incorporating diaphragmatic and slow nasal breathing into various daily activities, encompassing physical activities (e.g., speaking, swimming, walking, gardening), social activities (e.g., playing with children or pets), and work-related activities (e.g., managing work stress).
^
49
^

The phases of BRE will consist of: i) identification of the abnormal breathing pattern, ii) diaphragmatic breathing, ii) nose breathing, iii) slow breathing with controlled breath-holding at the end of exhalation, iv) adaptation of the new breathing pattern in everyday life activities and various positions (supine, semi-sitting, sitting), and v) breathing control in speech. The repetitions and sets of BRE are indicative, given that our priority was the progression and individualization during the sessions. For instance, the first session may only include recognition of the abnormal breathing pattern exercise and practice diaphragmatic and nose breathing retraining exercise. At the beginning of every session, each participant will be assessed for their compliance concerning the exercises (use of a calendar or via questions about their exercise). If a patient has not comprehended or cannot perform the exercises correctly, the previous session will have to be repeated. Once they have fully understood the instructions and execution, they will proceed to the subsequent BRE.

The
Table 1 illustrates the Key parameters of the rehabilitation program.

**Table 1. T1:** Key parameters of the rehabilitation program.

Intervention		Patient position	Instructions to participants	Time	Sets/Breathing cycles	Weekly repetition
**MDRT**		- Lie supine with relaxed limbs - 90 degrees flexion of the knees & hips		20-25 min	2S x 10BC	2/Week
**BRE**	**Recognition of the abnormal breathing pattern**	- A pillow between the knees & head. - Half-lying supine (45 degrees of spine flexion from the neutral supine position).	- *“Put one relaxed hand on your upper chest and the other on your stomach and clavicle”* - *“Breathe normally, slowly, in your own manner”* - *“Take a big breath”*	30 min	1S x 5BC	2/Week
	**Practice diaphragmatic and nose breathing retraining**	- Half-lying supine position - Pillows behind the head & knees - one relaxed hand over the stomach and the other on the upper chest and clavicle	- *“Close your mouth and try to breathe easily, slowly and softly through your nose”* - *“Be careful not to inhale with “big” breaths, try during inhalation to raise only the stomach”* - *“Exhalation is passive through the nose and lets your stomach fall gently”*		1S x 5BC	
	**Slow breathing and controlled breath holding after exhalation**	- Half-lying supine position - Pillows behind head and knees - One relaxed hand over stomach and the other on upper chest and clavicle	- *“Close your mouth and try to breathe easily, slowly and softly through your nose”* - *“Relax your shoulder & chest”* - *“Try to slow down your breaths”* - *“Sometimes it helps to count in your mind while you are breathing, e.g. breathe in for a slow count of 2 and breathe out for a slow count of 3until feel empty your stomach”* - *“Keep empty your stomach for 3-5 seconds”*		1S x 10BC	
	**New breathing pattern in everyday life activities and various positions**	- Supine - Semi-sitting - Sitting	- *“Try to breathe in and out slowly and through the nose, even in the most challenging conditions”* - *“You will be able to recognize faulty breathing patterns, and you will be able to correct them”* - *“Try to use a calendar or a mobile phone reminder to implement a diaphragmatic slow nose breathing pattern and breathing exercises”*		3S x 5BC	
	**Breathing control in speech**	- Supine - Semi-sitting - Sitting	- *“You must budget airflow to control the number of words you say per breath and the tone and loudness of particular words in a sentence”* - *“Apply a slow, through the nose, diaphragmatic breathing pattern at speech (max 4-6 words spoken during slow exhalation, with breathing pauses, and slow inhalations)”* - *“Breathe out so that your lungs feel empty, and, before inhaling again”* - *“At yawning and at sighing close your mouth”* - *“Poor voice quality (hoarseness, roughness, or a strained/strident voice) results from inadequate or badly controlled airflow. Speech prosody: rhythm and intonation”*		3S x 5BC	

Control Group: This group will receive only BRE, as mentioned in the intervention group.

